### Blinding to Intervention

In accordance with the CONSORT (Consolidated Standards of Reporting Trials) 2025 guidelines for cluster randomized trials [35], blinding will be implemented where feasible to minimize bias. As the AgF application leaves a distinct black stain on carious lesions, this may inadvertently reveal allocation status to participants, RACF staff, and treating clinicians. Therefore, no attempt will be made to blind the clinical team. To mitigate bias in outcome assessment, both site identity and treatment allocation will be blinded during data analysis. A detailed statistical analysis plan will be finalized, and analysis syntax prepared, prior to data availability. Data analysts will receive deidentified datasets with anonymized group labels (eg, Group A and Group B), and the allocation decoding key will be securely retained by the project lead until primary analyses are completed.

### Resident Participant Timeline

Table 1 presents the participant timeline for the cluster randomized controlled trial of AgF, including the intervention and control groups. Residents who elect to participate will be invited to provide informed consent. At baseline (T1), all participants will receive an oral health assessment and complete a demographic, quality of life, and oral health survey (Table 1). Those allocated to treatment will also receive an AgF application. At the 3-month follow-up, all participants will receive the oral health assessment and survey again; control group participants will receive the AgF application.

**Table 1. T1:** Resident participant timeline for the cluster randomized controlled trial of silver fluoride, showing intervention group and control group.

Procedures	Study period		
	Enrollment	T1	T2
Enrollment			
Consent (self, legal guardian, or NCAT^a^, QCAT^b^)	✓		
Exclusion criteria	✓		
Allocation (cluster)	✓		
Survey			
Demographics and oral health history		✓	✓
Quality of life (EQ-5D-5L) [36]		✓	✓
Geriatric Oral Health Assessment Index (GOHAI) [37]		✓	✓
Intervention			
Intervention clusters: AgF applications for clinically indicated teeth at T1		✓	
Control clusters: AgF applications for clinically indicated teeth at T2			✓
Summary of data collection			
Oral clinical assessment (dental caries experience; dentin exposure; tooth sensitivity; oral hygiene status; oral mucosal conditions; salivary status)		✓	✓
Oral health–related quality of life		✓	✓
Quality of life		✓	✓
Demographics	✓		
General health, medications, and diet		✓	✓
Health economic information: cost and referral uptake		✓	✓
Health economic information: participant experience		✓	✓

a NCAT: NSW Civil and Administrative Tribunal.

b QCAT: The Queensland Civil and Administrative Tribunal.

### Data Collection Methods

#### Resident Survey

Participants will be supported in completing a survey that asks about their oral health, quality of life, and demographic details (Table 1). These data will be used to test whether the oral health intervention affects outcomes relative to baseline and a nonintervention control.

Consented participants will be invited to complete the survey at baseline (T1) and again at follow-up (T2), using the workflow shown in Table 1.

For residents who are unable to complete the survey independently, appropriate support arrangements will be provided. Participants with physical, sensory, or literacy limitations who retain decision-making capacity may complete the survey with assistance from a trained member of the research team. In such cases, questions will be read aloud, and responses will be recorded verbatim without interpretation or prompting to minimize bias.

For residents who lack the capacity to provide responses independently, proxy responses may be obtained from a legally authorized representative or primary caregiver, where appropriate and with consent. The use of proxy respondents will be clearly documented in the dataset.

#### Oral Health Assessment

Along with the noninvasive M-OHAT undertaken by RACF staff, participants will also receive a noninvasive oral health assessment by an epidemiologically trained dental clinician (oral health professional). The research team will conduct data collection following a standardized protocol that includes an action plan for managing complications and distress where required.

The protocols for data collection will be based on methodologies from the National Study of Adult Oral Health [38]. Clinical examinations will be conducted by trained dental clinicians, using a mouth mirror and a periodontal probe under appropriate lighting conditions (headlight) to systematically assess oral health status. The oral health assessment will include evaluation of several domains. Soft tissue presentation will be assessed for the presence of ulceration, swelling, or suspicious mucosal lesions. Dry mouth will be recorded using the Challacombe index [39]. Gingival health will be assessed through visual signs of gingival inflammation. Oral hygiene status will be evaluated based on the presence of visible plaque or debris on tooth surfaces. The removable denture presentation will include recording whether dentures are present, their condition, and their level of cleanliness. Tooth status will be assessed at both coronal and root levels and recorded according to the presence of sound, decayed, filled, or missing teeth. Tooth mobility will be assessed clinically and recorded as present or absent. Oral pain will be recorded based on participant self-report or caregiver report, where applicable.[40] Dentin hypersensitivity will be assessed based on participant self-report or observable reactions to a gentle stream of air applied to tooth surfaces.

Residents may be assessed in their usual living environment, including while seated in a wheelchair, on a day recliner, in bed, or in a mobile dental chair depending on their mobility and comfort. This flexible approach ensures accessibility while maintaining standardized examination procedures. The research team will train a specialized team consisting of clinicians and data recorders. All study clinicians will receive training in conducting clinical assessments and applying AgF. Calibration sessions will be conducted to ensure high-quality data collection and comparability across all assessments.

After the oral health assessment, participants and their caregivers will be informed if any immediate oral or dental health concerns (eg, suspected oral mucosal lesions, symptomatic teeth causing acute pain, abscess, and/or draining sinus) are identified.

### Outcomes Measure of the Study

Based on the above assessment tools and collected data, oral health outcomes will include dental caries arrest, tooth sensitivity, oral pain, and quality-of-life outcomes. All these outcomes are specified as coprimary outcomes, as the intervention is designed to address multiple clinically meaningful domains of oral health in older adults. Given the multidimensional clinical intent of the intervention, these outcomes will be considered equally important in evaluating effectiveness.

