## Methods

### Trial Design

This study is part of a larger aged care full intervention package that assesses a combination of a modified oral health assessment tool (M-OHAT), standardized RACF staff training and education in using this assessment tool, standardized oral examination by an oral health professional, and an AgF intervention package to benefit the health and well-being of residents in RACFs. This study is designed as a cluster randomized controlled trial. RACFs serve as the unit of randomization, and individual residents as the unit of analysis. The control arm will receive a delayed intervention because of existing clinical equipoise regarding the effectiveness of AgF applications in reducing dentin hypersensitivity.

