### Sample Size Calculation

The primary outcome of AgF effects on dentin hypersensitivity was used for the sample size calculation. Based on estimates presented by Chan et al [23] and Castillo et al [32] assessing AgF effects on dentin hypersensitivity using a visual analog score, a mean difference of 2.9 units with a SD of 2.6 indicates that a total of 8 clusters (4 per arm) is required to achieve statistical power greater than .80 (*β*>.80), assuming a significance level of .05 (*α*=.05) and 25 participants per cluster. To account for potential attrition, we plan to increase the cluster size by at least 50%, resulting in 40 participants per cluster at baseline. This would yield 160 participants in each group, for a total of 320 participants.

Given the absence of known adverse health effects from AgF and the likelihood that participants will benefit from access to an otherwise unavailable health intervention, we propose overenrolling sites. Specifically, the aim is to recruit 28 clusters (14 per arm), with up to 40 participants per site. This will improve the precision of our estimates of efficacy. This oversampling is planned to account for potential within-facility clustering in residential aged care settings.

Assuming 25 participants per site complete both baseline and follow-up assessments and using a conservative intracluster correlation coefficient (ICC) of 0.15, this sample size will allow detection of an effect size of approximately 0.48 (Cohen *d*) [33]. For categorical outcomes, this sample would be powered at 0.80 to detect a 23% difference between groups, assuming a 50% control group proportion.

Using more precise parameters for this study design, 28 clusters with 25 individuals providing complete data and an individual autocorrelation of 0.5, the minimum detectable effect size decreases to 0.20 (mean difference divided by SD). For categorical outcomes, the same design would be powered at 0.80 to detect a 10% absolute difference, again assuming a control proportion of 0.5.

All sample size and power calculations were informed by Hemming et al [34] and conducted using the Shiny CRT Calculator: Power and Sample Size for Cluster Randomized Trials.

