#### Oral Health Status

Analyses will follow the intention-to-treat principle, whereby all participants will be analyzed according to their allocated cluster, regardless of adherence to the intervention. Generalized linear mixed-effects modeling will be used to quantify the treatment effect of AgF on oral health outcomes, including caries arrest, dental pain, and tooth sensitivity. If the extent of missing data exceeds acceptable thresholds, sensitivity analyses (eg, multiple imputation) will be conducted to assess the robustness of findings under different assumptions regarding missingness. Data from the intervention and control groups will be compared to estimate the treatment effect. These analyses will be undertaken at both the tooth or surface level and the participant level. Data from the standardized oral examination will provide caries status and tooth sensitivity at the tooth level, whereas pain and tooth sensitivity experiences at the participant level will be collected via visual analog scale and questionnaire on the presence of dental pain. Analyses will adjust for prespecified potential confounders at both resident and facility levels. Resident-level covariates will include age, sex, Aboriginal and Torres Strait Islander origin, baseline oral health measures, number of natural teeth, and relevant medical conditions where available. Facility-level factors, such as facility characteristics, will be considered where appropriate. These variables were selected a priori based on clinical relevance and existing literature. Baseline measures of the outcome variables, the time between T1 and T2, and other covariates relevant to each association of interest will be adjusted for in the analysis. The direction and magnitude of changes in the outcome measures, together with their respective CIs, will be estimated and reported.

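### The protocol sizes the trial on one primary outcome but declares four equally important coprimaries without saying whether any or all must succeed, so its detectable effects do not describe the declared primary analysis

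*Protocol article*

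**What the plan says.** Two current sections of the Protocol article describe the primary outcome differently.

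- **Sample Size Calculation:** "The primary outcome of AgF effects on dentin hypersensitivity was used for the sample size calculation". The base design rests on a visual analog score difference of 2.9 with SD 2.6, "assuming a significance level of .05", and concludes that "a total of 8 clusters (4 per arm) is required to achieve statistical power greater than .80". The enlarged design has 28 clusters with 25 completers each. At ICC 0.15 its detectable effect is given as about 0.48 SD, or 23 percentage points from a 50% control proportion. With an individual autocorrelation of 0.5 the figures become 0.20 SD and 10 points.
- **Outcomes Measure of the Study:** "oral health outcomes will include dental caries arrest, tooth sensitivity, oral pain, and quality-of-life outcomes". The section then says "All these outcomes are specified as coprimary outcomes" and that "these outcomes will be considered equally important in evaluating effectiveness".

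The outcomes section gives no any-of or all-of rule, no order and no split of alpha. The timeline table lists two quality-of-life instruments, GOHAI and EQ-5D-5L, and the outcomes section does not say which is the coprimary. On the clinical outcomes, the Oral Health Status section adds: "These analyses will be undertaken at both the tooth or surface level and the participant level".

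**The concern.** One sized primary and four equal coprimaries lead to different error rates and different power. Without a success rule, a reader cannot tell what result would count as showing effectiveness, or what chance the trial has of reaching it. The power statements in the Sample Size Calculation are per outcome and make no allowance for several primaries, so they fit neither way of reading four coprimaries. If one success is enough, testing each at 0.05 raises the chance of a false claim. If all four are needed, the chance of a true claim is lower than the 80% quoted.

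Timing adds weight. The Results section reports baseline and 3-month assessments complete in approximately 20 facilities as of February 2026. A choice of primary outcome or success rule is credible only if it is fixed before anyone can see results by arm.

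**Working it through.** **Inputs from the Sample Size Calculation:** 14 clusters per arm, 25 completers per cluster, ICC 0.15, power 0.80, alpha 0.05, planning effect 2.9/2.6 = 1.115 SD. The outcomes section supplies the number of coprimary domains, four.

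**Assumptions:** tests are two-sided. The 0.05 level, stated only for the 8-cluster design, also applies to the 28-cluster figures. The correlation between the four test statistics (rho) is not given, so a range from 0 to 0.9 is shown.

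**Step 1: reproduce the stated figures as single tests.**
- Design effect: 1 + (25 − 1) × 0.15 = 4.6. Effective n per arm: 14 × 25 / 4.6 = 350 / 4.6 = 76.1.
- SE of the standardised difference: sqrt(2 × 4.6 / 350) = 0.162.
- Detectable effect at 80% power: (1.960 + 0.842) × 0.162 = 0.454 by the normal approximation, and 0.472 by noncentral t with 26 df. The stated figure is about 0.48, where power is 0.84 (normal) or 0.81 (t).
- Binary outcome from 50%: 22.0 to 22.4 points, against 23 stated.
- The 8-cluster design at ICC 0.15 has power 0.86 (t, 6 df) or 0.96 (normal), consistent with the stated power above 0.80. The ICC behind that statement is not given.

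The stated figures are therefore what one outcome tested alone at 0.05 would give.

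**Step 2: one success suffices, each outcome tested at 0.05.**
- Independent outcomes: 1 − 0.95^4 = 0.185.
- Equicorrelated normal statistics, by simulation: 0.156 at rho 0.5 and 0.094 at rho 0.9.

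**Step 3: all four must succeed, each at 0.05 with 80% power.**
- Type I error stays at or below 0.05.
- Joint power if independent: 0.8^4 = 0.41. By simulation: 0.56 at rho 0.5 and 0.70 at rho 0.9.
- If hypersensitivity has the planned 1.115 SD effect, the expected test statistic is 1.115 / 0.162 = 6.9 and its power exceeds 0.999. Joint power is then set by the other three: 0.8^3 = 0.51 if independent, and 0.61 at rho 0.5.

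**Step 4: one success suffices, with familywise control at 0.05.** The strictest Holm step is 0.05 / 4 = 0.0125.
- Familywise error with all four at 0.0125, if independent: 1 − 0.9875^4 = 0.049.
- Detectable effect at that step, ICC 0.15: 0.54 (normal) or 0.58 (noncentral t), compared with 0.45 or 0.47 at 0.05.
- Binary outcome: 26 to 27 points instead of about 22.
- Power at 0.48 SD: 0.68 (normal) or 0.61 (t).
- Taking the protocol's more favourable 0.20 SD as given, the normal approximation moves it to 0.20 × (2.498 + 0.842) / (1.960 + 0.842) = 0.24.

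**The case against.** The sizing sentence can be read as naming the outcome used for the calculation, and sizing on one of several coprimaries is common practice. The Blinding to Intervention section promises an analysis plan and syntax before data are available, anonymised group labels, and a key held back until the primary analyses are done. A success rule and alpha allocation often sit in such a plan, which is not shown. The Oral Health Status section speaks of estimates with confidence intervals and sets no p-value criterion. All of this stands, and it limits the point. It does not remove it, because the number and rank of primary outcomes are fixed in the protocol itself and the two sections do not agree. A plan that chose one primary would contradict the equal-importance statement. One that kept four would leave the stated detectable effects describing something else.

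Three stronger readings are tempting and are not supported.
- **That the trial has several uncontrolled chances to claim success.** This holds only if any one success suffices, and the protocol does not say so.
- **That counting each level of analysis and each instrument gives seven primary tests and a 30% error rate.** The protocol declares four domains and does not make each level a coprimary. The 30% also assumes independence between tooth-level and participant-level results from the same residents.
- **That tooth-level models contradict the Trial Design statement that "RACFs serve as the unit of randomization, and individual residents as the unit of analysis".** Supplementary models at another level do not add primary tests by themselves.

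Nor can a collapse in power be claimed for this trial. The 41% assumes exactly 80% for every outcome, and no planning effects are given for the three outcomes other than hypersensitivity.

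**Conclusion.** The concern holds as an inconsistency within the protocol together with an unstated success rule. The detectable effects are single-test figures and do not describe the four-coprimary analysis that the outcomes section declares. The consequence depends on a rule the protocol does not give:

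- **Any-of:** familywise error of about 9% to 19%.
- **All-of:** type I error controlled, with joint power of about 41% to 70% at 80% per outcome, and higher if hypersensitivity has its planned effect.

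These sizes rest on two-sided tests, equal correlations from 0.9 to 0 between outcomes, and ICC 0.15. The familywise error does not depend on the ICC. The power cost is milder if the 0.20 SD figure applies. The planned blinded analysis lowers the risk of selective choice but does not settle which rule applies.

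**What to change.** Align the Sample Size Calculation and the Outcomes Measure of the Study before the allocation key is released:

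1. Keep the four coprimaries, which the protocol justifies by the multidimensional aim of the intervention.
2. Specify one participant-level test per domain, naming either GOHAI or EQ-5D-5L for quality of life.
3. State that success on any one outcome counts, under Holm at an overall 0.05.
4. Restate the detectable effects at the adjusted alpha: about 0.58 SD instead of 0.47 at the strictest 0.0125 step with ICC 0.15.
5. Label the tooth- and surface-level models as supportive.

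Naming the hypersensitivity visual analog score as sole primary, with the others as ordered secondaries, is an alternative for the sponsor to choose. It matches the sizing but demotes three declared coprimaries after follow-up is complete in many facilities. It also rests the trial on a self-rated scale in a population with much cognitive impairment.

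The recommended route needs no new data or sites. It costs wording and a less favourable stated detectable effect.

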### Calculation of Cost and Utility Weights

The health economic analysis will be based on cost-effectiveness and cost-utility analysis frameworks. The costs associated with the intervention will be estimated using a bottom-up approach. Costs will be estimated as the product of unit costs and the quantity of resources (labor, materials, and services) used in the activities of this study. The treatment cost will include oral health examination cost, AgF application, and costs for any urgent conditions (eg, acute infections), and calculations will be based on the schedule of fees by the Australian Government Department of Veterans’ Affairs [41]. The main effectiveness measure will be quality-adjusted life years (QALYs), and the utility weights to generate QALYs will be informed by the EQ-5D-5L scores and the Australian utility weights for the EQ-5D-5L [42]. The improvement of oral health status (eg, number of caries arrested) will also be assessed as a secondary effectiveness measure.

### Analytical Plan

Baseline measures of RACF and participant characteristics will be summarized to describe the group- and individual-level data*.* Demographic, clinical, and functional data will be summarized as mean (SD) or n (%) as appropriate.

#### Oral Health Status

Analyses will follow the intention-to-treat principle, whereby all participants will be analyzed according to their allocated cluster, regardless of adherence to the intervention. Generalized linear mixed-effects modeling will be used to quantify the treatment effect of AgF on oral health outcomes, including caries arrest, dental pain, and tooth sensitivity. If the extent of missing data exceeds acceptable thresholds, sensitivity analyses (eg, multiple imputation) will be conducted to assess the robustness of findings under different assumptions regarding missingness. Data from the intervention and control groups will be compared to estimate the treatment effect. These analyses will be undertaken at both the tooth or surface level and the participant level. Data from the standardized oral examination will provide caries status and tooth sensitivity at the tooth level, whereas pain and tooth sensitivity experiences at the participant level will be collected via visual analog scale and questionnaire on the presence of dental pain. Analyses will adjust for prespecified potential confounders at both resident and facility levels. Resident-level covariates will include age, sex, Aboriginal and Torres Strait Islander origin, baseline oral health measures, number of natural teeth, and relevant medical conditions where available. Facility-level factors, such as facility characteristics, will be considered where appropriate. These variables were selected a priori based on clinical relevance and existing literature. Baseline measures of the outcome variables, the time between T1 and T2, and other covariates relevant to each association of interest will be adjusted for in the analysis. The direction and magnitude of changes in the outcome measures, together with their respective CIs, will be estimated and reported.

#### Quality of Life Outcomes

Quality of life outcomes will be investigated using a similar analytic approach. Mixed-effects models will examine the effect of group on outcomes, alongside quantification of the effects of time and other covariates outlined above. Functional data at T2 may also be tested as moderators of treatment effect on outcomes.

Exploratory ancillary analyses may include post hoc examination of, or enrichment with, publicly available nonidentifying datasets. Demographic, clinical, or functional variables may be explored as longitudinal predictors or moderators using regression analyses. All data will be reported so that individual responses cannot be identified or reidentified in any way.

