## Introduction

### Background and Rationale

There are specific challenges in identifying and delivering effective treatments that can protect and improve oral health in residential aged care facilities (RACFs). The Australian Royal Commission into Aged Care Quality and Safety Final Report (2021) highlighted the neglect and consequences of oral health in residential aged care, and addressing this area of unmet need is critical [1]. In Australia, residential aged care is provided for older adults who can no longer live independently in their own homes. It includes accommodation and personal care 24 hours a day, as well as access to nursing and general health care services [2].

Older adults living in RACFs have a higher prevalence of poor oral health compared to older people living in the community. This population experiences untreated dental caries, estimated to be as high as 70% [3,4]. In addition, 82% of older adults have gingival recession (root exposure), which is a primary cause of dentin hypersensitivity [3]. Poor oral health causes pain and infection that are associated with major consequences for physical and mental health, including malnutrition, aspiration pneumonia, and cognitive decline [5,6]. Poor oral health can also more broadly impact quality of life by affecting the ability to eat, speak, and engage socially with others [7].

More than two-thirds of RACF residents live with moderate to severe cognitive impairment, further complicating their ability to maintain oral self-care and access conventional dental care [8]. Older Australians residing in RACFs also face various external barriers when accessing dental care. These include financial constraints, organizational barriers, and logistical barriers, which are further exacerbated by the complexity of the aged care system [9-15], particularly for those living in rural and regional areas of Australia. In addition, workforce shortages further restrict the availability of appropriate care [1,14].

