### Objectives

This study aims to evaluate the effectiveness of the AgF intervention in reducing tooth sensitivity and dental pain, arresting dental caries, and improving oral health and well-being among older adults residing in regional and rural RACFs. The study will also assess the economic impact and scalability of the intervention within aged care settings.

This study has the following objectives:

To evaluate the efficacy of a tailored AgF intervention in arresting caries and reducing dental pain and sensitivity among older adults in RACFsTo evaluate the efficacy of the AgF intervention in improving normal daily life activities and oral health–related quality of lifeTo evaluate the cost-effectiveness and cost-utility of the interventionTo evaluate scalability and facilitate the implementation of the developed full intervention package

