### Intervention

AgF will be the intervention treatment used in this study. The first of the 2 bottles of the SDI Riva Star Aqua system (manufactured by Southern Dental Industries Ltd.), which contains 38% aqueous AgF, will be applied. This corresponds to step 1 of the manufacturer’s 2-step procedure. The decision to use only the first bottle is intended to simplify the application process and reduce treatment time. Using the first bottle of AgF ensures the evidence is relevant for generic AgF products, which is important for wider implementation of the findings.

At time 1 (the initial appointment, T1), all consented participants will undergo an oral examination to assess oral conditions and identify teeth requiring AgF treatment.

In an oral environment with a high risk of caries (eg, salivary gland hypofunction, acidic mouth pH), root surfaces and exposed dentin are at increased risk of dental caries developing. For participants assessed as being at high-risk of oral health issues developing, referral and discussion with the nurse coordinator at the facility will be undertaken as appropriate.

Participants in the intervention group will receive AgF during this first appointment. In contrast, participants in the control group will receive the same treatment at the 3-month follow-up appointment. AgF will be applied by the research team’s trained oral health professionals.

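### Functional data measured at T2, after treatment, are named as possible effect moderators; the moderator should be taken at T1 (baseline)

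*Protocol article*

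**What the plan says.** The Quality of Life Outcomes section of the Protocol article describes mixed-effects models for the effect of group and then adds: "Functional data at T2 may also be tested as moderators of treatment effect on outcomes". The next paragraph allows functional variables, among others, to be explored as predictors or moderators, without naming a time point.

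The timing of treatment is clear. The Intervention section states: "Participants in the intervention group will receive AgF during this first appointment"; by contrast, "participants in the control group will receive the same treatment at the 3-month follow-up appointment". The Resident Participant Timeline adds: "At the 3-month follow-up, all participants will receive the oral health assessment and survey again".

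Two passages link function to treatment. The second objective includes "improving normal daily life activities", and Background and Rationale says that poor oral health reduces quality of life by "affecting the ability to eat, speak, and engage socially with others".

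On baseline data, the opening of the Analytical Plan refers to baseline measures and continues: "Demographic, clinical, and functional data will be summarized". Table 1 schedules EQ-5D-5L and GOHAI at both T1 and T2. It lists no separate functional instrument, and the article does not define functional data.

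**The concern.** A moderator should be a characteristic that treatment cannot have altered. Residents with the same baseline function are comparable between arms because facilities were randomised. Residents with the same T2 function need not be. Some treated residents may be in the high-function group only because AgF put them there, and they would then be compared with controls who reached that level untreated.

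This is a time point written into the plan, not a detail left for the SAP. Nothing in the article restricts moderators to baseline or offers a method for moderators measured after randomisation. At stake are the statements about which residents benefit more or less. The overall estimate of whether AgF works does not depend on this analysis.

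**Working it through.** The plan gives no figure to reproduce. The check has two parts: the timing, and an illustration of what the timing could do.

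**Timing.** AgF is given at T1 in the intervention arm and at T2 in the control arm. Exposure therefore differs throughout T1 to T2. Function and outcomes at T2 are recorded at the end of that period, at one visit. On the trial's own second objective, T2 function may be a consequence of allocation.

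**General formula.** Let τ be the true effect on the outcome, δ the effect of AgF on T2 function, and β the within-arm slope of outcome on T2 function. In a linear model with a uniform shift, the treatment coefficient at fixed T2 function is τ − βδ. It equals τ if δ = 0 or β = 0.

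**Hand example (inputs assumed).** Function = 0.5A + U + error and outcome = 0.48A + 0.5U + error, where A is the arm, U is an unmeasured health factor, and U and the function error have variance 1. Then:

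- β = 0.5 × 1/(1 + 1) = 0.25
- βδ = 0.25 × 0.5 = 0.125
- conditional coefficient = 0.48 − 0.125 = 0.355, which is 0.125/0.48 = 26% below the truth

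The 0.48 is the detectable effect in the Sample Size Calculation, not an expected effect. Set against that section's planning effect for hypersensitivity (2.9/2.6 = 1.12 SD), the same 0.125 is about 11%. With δ = 0 it is 0%. In this model the coefficient is 0.355 at every level of function, so the group-by-function interaction is exactly zero.

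**Simulation.** The design values come from the Sample Size Calculation: 28 clusters, 25 completers each, ICC 0.15. The true effect is 0.48 SD for every resident, with 400 replicates. The rest is assumed:

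- u (frailty) and e are standard normal
- T1 function = 0.7u + noise (SD 0.714)
- T2 function = 0.7u + 0.4e + noise (SD 0.59) + the AgF shift
- outcome = 0.48A + cluster effect + √0.85 × (0.5u + √0.75 × e)
- an uneven shift is confined to the frailer half (u < 0) and is doubled there, so the average shift is the same

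| Average AgF shift in T2 function | T1 split: low / high | T2 split: low / high | T2 continuous: treatment coefficient / interaction |
|---|---|---|---|
| 0 | 0.481 / 0.478 | 0.478 / 0.477 | 0.477 / −0.005 |
| 0.25, uniform | 0.495 / 0.487 | 0.389 / 0.394 | 0.332 / 0.000 |
| 0.25, uneven | 0.475 / 0.474 | 0.378 / 0.342 | 0.296 / 0.059 |
| 0.5, uniform | 0.475 / 0.488 | 0.264 / 0.294 | 0.162 / −0.004 |
| 0.5, uneven | 0.487 / 0.482 | 0.334 / 0.214 | 0.149 / 0.020 |

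The simulation error of an overall effect is about √[(2/14)(0.15 + 0.85/25)]/√400 = 0.162/20 = 0.008.

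**Check against the formula.** Here β = √0.85 × (0.5 × 0.7 + √0.75 × 0.4)/(0.7² + 0.4² + 0.59²) = 0.642/0.998 = 0.643. For uniform shifts, τ − βδ is 0.48 − 0.643 × 0.25 = 0.319 and 0.48 − 0.643 × 0.5 = 0.158. The simulated values are 0.332 and 0.162.

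**Reading.** Under a uniform shift the subgroup effects fall but the interaction stays near zero. Under an uneven shift a false difference appears: 0.334 − 0.214 = 0.12 at an average shift of 0.5. Its direction depends on coding. The split shows the larger effect at low function, while the linear interaction is slightly positive. With the T1 moderator, all effects lie between 0.47 and 0.50.

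**The case against.** Several points on the other side are sound.

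- **The bias is conditional.** If AgF does not alter T2 function, the simulation shows none. Under a uniform shift the interaction test itself reports no moderation. A false subgroup difference needs an uneven shift, which is assumed here.
- **The percentage is not a forecast.** A reader might take 26% as the expected bias. The document supplies neither the effect on function nor its relation to the outcome. The simulation also assumes a strong relation (slope 0.643).
- **Functional data are undefined.** Treating them as the daily-life activities in the objectives is an inference. If they mean general mobility or dependency, AgF may have little effect on them.
- **The analysis is optional.** The sentence permits the test and does not require it, and a detailed SAP is promised before data are available.

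These limit the size and weight of the point but do not remove it. The time point is stated, the article's own objective supplies the mechanism, and a baseline moderator avoids the problem whichever definition applies.

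A reader might also extend the argument to the adjustment in Oral Health Status, where "the time between T1 and T2, and other covariates relevant to each association of interest will be adjusted for", and conclude that the T1–T2 interval should leave the main model. The document does not support that. The interval is recorded after randomisation, but no passage shows that treatment affects it, and the study coordinator arranges the 3-month visits with no stated difference by arm. If intervals differed through scheduling alone and time affected the outcome, dropping the term could leave bias in.

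**Conclusion.** The point holds as a correction to a secondary analysis. Testing T2 function as a moderator conditions on something measured after about 3 months of differential exposure, in a domain the trial may be trying to change. Subgroup-specific effects could be biased, and a false subgroup difference could arise if AgF changes function unevenly.

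No size can be fixed from the document. In the illustrations, bias runs from zero (no effect on function) to subgroup estimates of 0.21 to 0.33 against a true 0.48 (average shift 0.5). These figures rest on assumed relations between function, frailty and outcome.

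Two wider inferences are not supported: that the planned interaction test will necessarily show false heterogeneity, and that the main results are compromised. The main treatment-effect estimates do not use this moderator.

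**What to change.** In Quality of Life Outcomes, change the time point of the functional data from T2 to T1 (baseline) and test the group-by-baseline-function interaction. Name the measure and choose one scheduled at T1, for example EQ-5D-5L or GOHAI items. Apply the same baseline restriction to moderators in the exploratory paragraph that follows; otherwise functional variables could still enter there at any time point. If T2 function is of interest, analyse it as an outcome, or in a mediation analysis with its assumptions stated.

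The cost is a change of wording, best made while the SAP is being finalised. No new data are needed if the measure comes from the surveys already scheduled at both visits. If functional data mean something recorded only at T2, no baseline version exists and the moderator test should be dropped. The adjustment for the T1–T2 interval need not change.
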